#### Quality assurance

As a minimum, derivation of each of the primary outcomes will be undertaken twice, independently, with primary analyses also performed twice, independently. Dependent on capacity, derivation of key secondary outcomes will also be undertaken twice, independently where possible.

### Missing data (28)

To account for the hierarchical structure of the data (with individuals nested within families, and families within clusters), we will employ a two-level ‘wide’ multiple imputation strategy utilising fully conditional specifications. This approach allows us to impute missing data by specifying a model that includes intervention effects and stratifiers at the cluster level (level 2), along with the relevant baseline person-level predictors at the individual level (level 1). This approach requires ignoring possible clustering of standard errors. An example is where more than one caregiver is recruited in a household, therefore generating biased estimates of ICCs. As the substantive variance partition of interest is at level three, the impact of this would likely be negligible. A consistent imputation rule will be used to determine where scales are imputed, items are imputed, or another strategy is used.

### Additional analyses (29)

#### Gender-disaggregated analyses

Specific outcomes described in Tables 1, 2, and 3 will be analysed disaggregated by caregiver or adolescent gender. These will be estimated as unadjusted models including terms for stratification, time, and intervention-by-time only.

**Table 1 Tab1:** Primary outcomes

Outcome	Informant	Gender disaggregated	Measure
Child maltreatment includes both physical and emotional abuse	Both	No	Caregiver and Child Versions of the International Society for the Prevention of Child Abuse and Neglect Screen Tool for Trials (ICAST-Trials) [17] (CG Range 0–140; AD Range 0–140)
Child physical abuse	Both	No	ICAST-Trial Caregiver and Child Versions Physical Abuse subscale [17] (CG Range 0–40; AD Range 0–40)
Child emotional abuse	Both	No	ICAST-Trial Caregiver and Child Versions Emotional Abuse subscale [17] (CG Range 0–100; AD Range 0–100)
Sexual violence victimisation and vulnerability	Both	Yes (adolescent)	Combining items of the ICAST-Trial Caregiver and Child Versions of Contact and Non-Contact Sexual Abuse subscale, Alcohol-Facilitated Forced Sex subscale [17], the WHO’s Violence Against Women Instrument and Global Partnership to End Violence Against Children’s Disrupting Harm Project Transactional Sex items. The CDC Violence Against Children and Youth Surveys [18], and a locally derived sexual violence vulnerability scale developed through consultation with families and practitioners (CG Range 0–90; AD Range 0–180)
Sexual violence victimisation	Adolescent	Yes (adolescent)	ICAST-Trial Caregiver and Child Versions of Contact and Non-Contact Sexual Abuse subscale, Alcohol-Facilitated Forced Sex [17], the WHO’s Violence Against Women Instrument Transactional Sex item and Global Partnership to End Violence Against Children’s Disrupting Harm project instrument (AD Range 0–90)
Sexual violence vulnerability	Both	Yes (adolescent)	CDC Violence Against Children and Youth Surveys [18], and a locally derived sexual violence vulnerability scale developed through consultation with families and practitioners (CG Range 0–90; AD Range 0–90)

**Table 2 Tab2:** Secondary outcomes

Outcome	Informant	Gender disaggregated	Measure
Parental supervision, inconsistent discipline, positive parenting, positive involved parenting	Both	No	Alabama Parenting Questionnaire subscales [29] (CG Range 0–310; AD Range 0–310)
Child neglect	Both	No	ICAST-Trial Caregiver and Child Versions Neglect subscale [17] (adapted for low-income contexts where neglect may be unintentional/poverty-related) (CG Range 0–30; AD Range 0–60)
Caregiver and adolescent attitudes to physical punishment	Caregiver	No	UNICEF Multiple Indicator Cluster Surveys (MICS) 5 Child Discipline module [26] (CG Range 0–10)
Sexual violence victimisation risk planning	Both	No	Scale developed for a PLH RCT in South Africa [12] (single item) (CG Range 0–10; AD Range 0–10)
Intimate partner violence (IPV) experience, witnessing (adolescent report only), and perpetration (caregiver report only)	Both	Yes (except for witnessing)	WHO’s Violence Against Women Instrument (VAWI) [30] (adapted) ICAST-Trial Child Version [17] (select items) (CG Range 0–100; AD Range 0–120)
Gender equitable behaviours (caregiver report only)	Caregiver	Yes (caregiver)	Survey developed by researchers at the London School of Hygiene and Tropical Medicine (LSHTM); used in an RCT of a violence prevention intervention in Tanzania [31]. Survey developed by researchers of an RCT of a gender-transformative violence prevention intervention in Rwanda [32] (CG Range 0–40)
Caregiver and adolescent attitudes towards gender roles	Both	Yes (informant)	Attitudes toward gender roles section of the WHO Multi-Country Study on Domestic Violence [30] (CG Range 0–60; AD Range 0–60)
Caregiver support for school	Caregiver	No	Parent involvement and support of education [33] (CG Range 0–50)
Parent communication	Caregiver	No	Fast Track Intervention Study’s Parent-Child Communication Scale [34] (adapted) (CG Range 0–60)
Economic hardship	Both	No	Monthly shortfalls of basic necessities, such as clothes, soap, and school equipment (CG Range 0–8; AD Range 0–80)
Financial self-efficacy [9h] and family financial management	Both	No	Items on borrowing (from loan sharks and others), saving, and budgeting (CG Range 0–30; AD Range 0–30)
Parenting stress	Caregiver	No	Parental Stress Scale [35] (CG Range 0–70)
Mental health distress	Both	No	Patient Health Questionnaire 4 (PHQ-4) [36] (CG Range 0–40; AD Range 0–40)
Social support	Both	No	Medical Outcomes Study Social Support Survey [37] (CG Range 0–80; AD Range 0–80)
Sexual risk behaviour	Adolescent	Yes (adolescent)	CDC Violence Against Children and Youth Surveys (VACS) [18]. South African Demographic and Health Survey [38]. One item on age-disparate sex (AD Range 0–30)

**Table 3 Tab3:** Exploratory outcomes

Outcome	Informant	Gender disaggregated	Measure
Use of internet and exposure to online violence risk	Both	No	The Global Partnership to End Violence Against Children’s Disrupting Harm project [19] (adapted) (CG Range 0–20; AD range 0–110)
Digital literacy	Both	No	Questions developed by the research team to assess digital skills (CG Range 0–40; AD Range 0–40)
Adolescent externalising and internalising behaviour	Caregiver	No	The Child and Adolescent Behavior Inventory (CABI) [20] (CG Range 0–140)
Substance use	Both	No	WHO Alcohol Use Disorders Identification Test [21] and the WHO Global School-based Health Survey [22] (adapted) (CG Range 0–20; AD Range 0–20)
Engaged responsive parenting	Both	No	Encompassing cross-cultural indicators of playful learning [23], characteristics of learning through play [24, 25] and positive parenting. Measures include the APQ positive parenting and involvement subscales, the parent-child communication scale, and parent support for school. Caregiver’s engagement with playful activities in the app (e.g. number of playful activities completed) will be measured through app engagement data (CG Range 0–260; AD Range 0–150)

#### Methods for additional analyses

The trial extends the analysis to investigate the effects of the intervention by mediation, moderation and community spread. The goal of these additional analyses is to explore the pathways through which the intervention impacts specific outcomes, to understand the conditions where these effects are amplified or attenuated, and how the intervention’s impact spreads within the community.

Mediation analysis will be conducted in instances where a significant effect of the intervention on both a potential mediator at post-intervention and on a primary outcome at the 12-month follow-up stage is observed. Utilising a two-level model that include individuals nested within clusters, our approach will incorporate a 2-1-1 mediation framework [39]. The mediation model will explore the interactions between the intervention allocation and the cluster-level mean of the mediator, together with outcome’s cluster-level random intercept at the 12-month follow-up, adjusting for baseline characteristics. The differentiation of pathways between the mediator and outcome, at both the individual and cluster level, will allow us to identify any contextual mediating effects.

The aim of the moderation analysis is to explore differential effects of the intervention, considering both the individual-level and cluster-level characteristics. The analysis will mirror the vector of level 2 characteristics used in the main outcome models. By centring the moderators within their context and examining the interactions at both levels within our hierarchical data structure, we will be able to identify variations in the intervention’s efficacy across different groups and contexts. Where feasible with data structures, moderated mediation hypothesis testing will be conducted using a multiple-group multilevel structural equation modelling approach [40]. Using level 3 variables as stratifiers, we will rerun mediation models to assess whether pathways comprising indirect effects are different over strata. The final analytic plans for mediation and moderation analyses will be submitted to Open Science Framework a priori to conducting these analyses.

Finally, we will examine community spread using standard indicators of intervention exposure in follow-up surveys. We will report descriptive statistics characterising the extent of intervention exposure in control clusters. If appropriate, we will use a multilevel complier average causal effect analysis to recover the ‘true’ effect of exposure to the intervention, focusing on primary outcomes and considering intervention exposure for each timepoint.

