### Objectives (8)

The SAP is guided by the trial objectives, informing the choice of statistical methods, the handling of data, and the interpretation of results. The trial has the following objectives:Determine the effectiveness of the ParentApp intervention by assessing if the intervention, compared to a control condition (WashApp), effectively decreases rates of adolescent maltreatment (physical and emotional abuse) and sexual violence victimisation and vulnerability at 1 month and 12 months post-interventionEvaluate cost-effectiveness by analysing the economic viability of the ParentApp intervention by analysing its cost-effectiveness in achieving the primary and secondary outcomes, from a perspective that encompasses the public and health sector, and participant costs and benefitsAssess scalability and delivery by investigating the feasibility of delivering ParentApp at scale through local implementing partners, focusing on the programme’s accessibility and participant engagement within the Tanzanian contextExplore possible mechanisms of change through mediation and moderation analyses. To identify pathways through which ParentApp impacts behavioural outcomes, including changes in parenting practices, adolescent behaviour, and family dynamics

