### Sample size (11)

The sample size is based on a detailed power calculation informed by preliminary pilot study data, using generalised Poisson linear mixed-effect models. These calculations posit that, to achieve a statistical power of 80% against an anticipated effect size of 0.95 and a control group mean outcome of 4, while accounting for potential attrition rates within both the control and intervention arms, a minimum ensemble of 80 clusters, each comprising 30 dyads, is required. The trial will therefore enrol a cohort of approximately 2400 caregiver-adolescent dyads or 4800 participants.

A subset of participants, comprising 40 to 60 caregivers and 20 to 30 adolescents, will be invited to engage in post-intervention qualitative interviews. These discussions are aimed at eliciting in-depth insights into the experiential dimensions of the programme, thereby enriching the quantitative data. Additionally, semi-structured interviews will be conducted with a representative sample of 10 implementing staff members, offering a comprehensive perspective on programme delivery dynamics.

Expanding the impact of the study, we intend to include adolescent siblings or co-resident adolescents present within approximately 50% of the participating households (estimated *n* = 2610) in the post-intervention assessment phase. This strategic inclusion aims to ascertain the broader familial impact of the intervention, thereby capturing any auxiliary effects on the household’s adolescent population not directly involved in the primary intervention activities.

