### Statistical interim analyses and stopping guidance (13a, b, c)

Interim analyses will be conducted at 1 month post-intervention (4 months post-baseline). During the interim analysis, the nominal significance has been set at *p* < 0.001 to mitigate the risk of type I error or false-positive findings due to multiple testing across the trial’s timeframe. The residual nominal significance level for the final analyses will thus approximate *p* = 0.05. As such, while 95% confidence intervals will be calculated to facilitate the interpretation of the interim results, these results will not be used to make conclusive statements about the intervention’s effectiveness.

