## Statistical principles

### Confidence intervals and p values (16, 17, 18)

All reported confidence intervals will be at the 95% level. Any hypothesis testing will be undertaken at the level of statistical significance corresponding to the prespecified alpha level of *α* = 0.05 with two-tailed tests for all analyses. Minimal clinically important differences are not well understood or established for many outcomes included in this analysis. Therefore, we will not explicitly benchmark findings against these differences in any primary analyses.

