The intervention’s effectiveness will be evaluated through multiparameter Wald tests or likelihood ratio tests as appropriate, comparing models with and without intervention-by-time interactions to assess the totality of the intervention’s impact. Furthermore, the use of Wald tests will assess the significance of specific fixed effects model coefficients, particularly in relation to the intervention-by-time interactions. In addition to the primary analysis, we will conduct both adjusted analyses with unimputed data and unadjusted analyses with unimputed data, which include terms for stratification, time, and intervention-by-time, to provide a baseline estimate of intervention effectiveness without covariate adjustments.

Both Wald tests and marginal effects plots will be used to evaluate differences of outcome interactions by intervention group and will be supported by the computation of intra-cluster correlation coefficient (ICC) for hierarchical data. Depending on the distribution of the data, i.e. binary or Poisson, median incidence rate ratios (IRR) or odds ratios for hierarchical and non-normally distributed data will be respectively calculated.

The *p*-value threshold will be 0.05 for all pre-specified analyses. However, due to multiple comparisons planned for exploratory analyses, a sharpened *q*-value will be used with respect to all exploratory analyses to adjust the *p*-value threshold for statistical significance to reduce the likelihood of false positives.

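### Mediation is run only for pairs with a significant mediator effect and a significant 12-month outcome effect, which can hide real pathways and overstates the size of those reported

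*Protocol article*

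**What the plan says.** The fourth trial objective is to explore "possible mechanisms of change through mediation and moderation analyses" (Objectives). Methods for additional analyses then sets the rule for when mediation is done: "Mediation analysis will be conducted in instances where a significant effect of the intervention on both a potential mediator at post-intervention". The second half of the condition is that the intervention effect on some primary outcome is significant at 12 months. For pairs that pass, the plan is a 2-1-1 model with individuals nested in clusters. No mediation analysis outside this gate is described, and neither is any allowance for the selection. Moderated mediation reruns the mediation models within strata, so it appears to inherit the gate. Moderation alone carries no such condition. The detailed mediation and moderation plans are to be filed on the Open Science Framework before those analyses are done.

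On significance levels, tests are two-sided ("with two-tailed tests for all analyses"), and the p-value "threshold will be 0.05 for all pre-specified analyses". Exploratory analyses use a sharpened q-value.

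**The concern.** The rule asks for a significant total effect before an indirect effect is estimated. The total effect is the sum of the indirect effect and everything else the intervention does. If another path works in the opposite direction, the total can be near zero while the mediated path is real. Even when the mediator carries the whole effect, the total-effect test can be much weaker than the tests of the two component paths. A trial in which parenting improves but abuse does not measurably fall is one where the indirect effect is of particular interest, and the rule rules it out.

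The mediator half of the gate does different damage. The estimate that passes the test is the same estimate that enters the product forming the indirect effect. Keeping only significant values of it pushes its average upward.

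**Working it through.** **The plan's own figures.** The article gives no figure for mediation. The nearest is the sample-size statement, "to achieve a statistical power of 80% against an anticipated effect size of 0.95 and a control group mean outcome of 4", for which "a minimum ensemble of 80 clusters, each comprising 30 dyads, is required". Reading 0.95 as a rate ratio, with a two-sided test at one follow-up and no clustering, n per arm = (1.960 + 0.842)² × (1/4 + 1/3.8) / (ln 0.95)² = 1531, and 1200 per arm gives 69.9% power. Pooling two follow-up waves at an intracluster correlation of 0.02 gives 79.7%. The correlation, the attrition rate and the effect scale are not stated, so the 80% can be neither confirmed nor called wrong. It is used below only as one assumed power for the outcome test. All mediator powers are assumptions.

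**Step 1: how often the gate opens for one real pair.** If the two tests are independent, P(open) = power of mediator test × power of outcome test.
- 80% and 80%: 0.80 × 0.80 = 0.64, so 36% of real pairs are never analysed.
- 50% and 50%: 0.50 × 0.50 = 0.25, so 75% are never analysed.

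**Step 2: overstatement of the treatment-to-mediator path.** Let the z-statistic be normal with mean d = 1.96 + z(power) and unit variance. Given z > 1.96, the ratio of the expected to the true value is 1 + φ(1.96 − d) / (power × d).
- 80% power: d = 2.80, ratio = 1 + 0.280/(0.80 × 2.80) = 1.13.
- 50% power: d = 1.96, ratio = 1 + 0.399/(0.50 × 1.96) = 1.41.
- 30% power: ratio = 1.81.

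**Step 3: simulation of the whole rule.** There were 4000 runs with 80 clusters, 28 people retained in each, intracluster correlation 0.05, mediator-to-outcome coefficient b = 0.5, and continuous measures. The treatment-to-mediator effect is a, the direct effect is c′, and the true indirect effect is a × 0.5. The comparison is an ungated test requiring both the a and b paths to be significant.

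| Scenario | Mediator power | Total-effect power | Gate opens | Ungated test detects | Share of those detections the gate blocks | Mean indirect effect, all runs → runs passing the gate |
|---|---|---|---|---|---|---|
| a 0.184, c′ 0.112 | 80% | 81% | 68% | 79% | 14% | 0.092 → 0.105 (+14%) |
| a 0.184, c′ 0.045 | 81% | 47% | 43% | 80% | 47% | 0.092 → 0.108 (+17%) |
| a 0.130, c′ 0.139 | 51% | 79% | 46% | 50% | 11% | 0.064 → 0.089 (+39%) |
| Full mediation: a 0.184, c′ 0 | 80% | 24% | 22% | 79% | 72% | 0.092 → 0.113 (+23%) |
| Opposing paths: a 0.25, c′ −0.12 | 97% | 5% | 4% | 96% | 95% | 0.125 → 0.128 (+2%) |

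Averaged over all runs, the estimate is unbiased (0.092 for a true 0.092).

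**Step 4: false pathways.** With no treatment-to-mediator effect, the gate passes in 3.7% of runs, and a pathway is both passed and declared in 3.6%. With no mediator-to-outcome effect, the corresponding declared figure is 3.5%. The ungated test declares 5.0% and 4.2%. The gate does not raise the error rate per pair.

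**Step 5: is the gate the only source of the bias?** No. In the first scenario, dropping the gate but reporting only pathways significant on the ungated test gives a mean of 0.104, against 0.105 with the gate.

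**The case against.** The analyses are exploratory and their final form is deferred to a later filing. The stated aim is to learn how the intervention produces its effects, so requiring an observed effect first is coherent and limits multiplicity. Table 1 has six rows, five with two informants, which makes 5 × 2 + 1 = 11 outcome-informant combinations for every mediator. The multiplicity point stands and argues for a short pre-specified list. The deferral does not rescue the rule: nothing says the later filing will drop it, and the article states it affirmatively.

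It is also fair that at 80% power for both tests the gate blocks only 14% of the pathways an ungated test would detect. The serious losses come when the total effect is weakly powered or paths oppose.

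Three stronger readings are tempting, and the documents do not support them.
- A reader might infer that the gate has two competing thresholds, because for the 1-month wave the plan says "During the interim analysis, the nominal significance has been set at" 0.001. That level is confined to the interim look. The gate needs 12-month data, which are analysed after database lock, where 0.05 applies.
- A reader might infer that the mechanism objective will often go unanswered. The closure figures apply to one mediator-outcome pair. There are several primary outcomes, 15 rows of secondary outcomes from which mediators could come, and moderation is ungated. Effects on mediators that are secondary outcomes are also estimated by the main models whatever the primary result.
- A reader might infer more false pathways. Step 4 shows otherwise; the inflation is in effect size.

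**Conclusion.** The point holds in this form: the double significance gate can leave real pathways unestimated and makes the indirect effects that are reported too large on average. At an assumed 80% power for each test, about a third of real pairs go unanalysed, rising to more than half when either power is near 50%. Overstatement is about 13 to 14% at 80% power and about 40% at 50% mediator power. The simulated figures depend on the assumed intracluster correlation, path coefficient and continuous measures. The direction of both effects does not depend on these values, but the size does. The matter is exploratory but bears on a stated objective, so the rule should be changed before the mediation plan is filed.

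**What to change.** In the mediation plan to be filed on the Open Science Framework:
- remove the requirement that either effect be significant;
- name in advance a limited set of theory-based mediators and primary outcomes, starting from the domains listed in the fourth objective (parenting practices, adolescent behaviour, family dynamics);
- estimate and report the 2-1-1 indirect effect with a confidence interval for every pre-specified pair, whatever the p-values for the mediator and the total effect;
- attach the sharpened q-value already planned for exploratory analyses, and use it to label results, not to decide which are shown. Showing only the significant ones would bring the bias back (Step 5).

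No new data are needed. The cost is revised wording, additional models and a longer set of exploratory results. Keeping the list of pairs short contains it.
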